**Treatment Assignment and/or Randomization**

If participants meet eligibility criteria and a signed consent form has been received from a parent/guardian, they may be contacted and scheduled for a baseline session. For participants aged 18 years, baseline sessions may be scheduled prior to obtaining consent (as consent will be obtained at baseline prior to administering any study procedures). For all participants, a member of the study team will discuss the consent/assent form with the participant, provide answers to any questions, and, if the participant is interested, a licensed clinician will obtain informed consent/assent. The participant will then be given a signed copy of the consent/assent form.

Once enrolled and after the baseline phase (EMA Phase 1; Baseline as Usual), participants will be scheduled for randomization, which will employ a 2-arm, within-subject, parallel group design to examine effects of short- and longer-term withdrawal across 8 weeks of cannabis abstinence on depression and SI. Participants will be randomized to 8 weeks of abstinence with contingency management (CB-Abst: n=100) or non-contingent monitoring with no abstinence requirement (CB-Mon: n=100) using a 1:1 ratio in blocks of 6. A subset of study staff who will administer surveys and questionnaires querying about mood and suicidality will be blind to group assignment. Randomization will be based on a computerized scheme developed by the study statistician. Randomization will be stratified by age (<=14 years old vs >=15 years old), sex (male vs female), and depression severity (mild/moderate vs. Moderately severe/severe). A key aspect of the approach is that the 8-week period is long enough to observe true changes due to cannabis discontinuation, separate from effects of cannabis withdrawal and residual cannabinoid exposure. Groups will complete 1-week of EMA in weeks 1 (EMA Phase 2; Randomized Withdrawal) and 8 (EMA Phase 3; Randomized Sustained Abstinence) of the randomized study period.

Individuals randomized to monitoring who incidentally stop using cannabis, or express an interest in discontinuing cannabis, will not be removed from the study. If desired, these individuals will be provided with substance use resources at the time of interest in cessation.

1. **STUDY PROCEDURES**

Study procedures are nearly identical to those used in IRB approved pilot protocol (#2021P002416).

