**Data analysis.**

**Aim 1: To test if negative mood and SI are temporarily relieved and stabilized through acute cannabis use (i.e., negative reinforcement cycle).** We will only use phase 1 data, the 2-week baseline period in which all participants may use cannabis. *Hypothesis 1.1:* We hypothesize that negative affect measures for a) the current random prompt, and b) the prior random prompt (a lag-1 term) will predict 1) greater cannabis use independent of motivating reason (i.e., lower probability for the zero component of the model), and 2) higher scores for motivated cannabis use to improve negative mood. Negative affect measures will therefore be converted to z-scores for this analysis and included as predictors for both the zero and non-zero components of the model. *Hypothesis 1.2:* We hypothesize that the binary indicator for cannabis use in the last hour will predict lower, less variable scores for the negative affect measures. Therefore, the binary use indicator will be included as a predictor for the beta regression residual variance term as well. *Hypothesis 1.3 (exploratory):* There will be within-subject correlates (e.g., concurrent other substance use, social context of use) and between-subject factors (e.g., cannabis use and depression severity, history of suicidal behavior) that moderate relationships between acute cannabis use and negative affect.

**Aim 2: To test if negative mood and SI initially increase with the start of abstinence and then decrease in both mean levels and variability after cannabis wash-out.** We will use phase 1 – 3 data, including predictors for a) group differences (CB-Abst vs. CB-Mon), b) differences by phase (phase 3 vs. phase 1 and phase 2 vs. phase 1), and c) terms for the group by phase interactions. All terms will be included as predictors for the beta regression residual variance term as well. We will only include data for the CB-Abst group with confirmed abstinence for phases 2 – 3. *Hypothesis 2.1:* We hypothesize that CB-Abst will show higher mean negative affect scores and greater variability during phase 2 compared to phase 1, while CB-Mon will show no differences between phases. *Hypothesis 2.2:* We hypothesize that CB-Abst will show lower mean negative affect scores and less variability during phase 3 compared to phase 1, while CB-Mon will show no differences between phases.

**Exploratory analyses:** To further assess heterogeneity in suicidal ideation, we will conduct a set of

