**Protocol non-adherence.** Analyses involving phase 1 and/or phase 2 of EMA data collection, will only consider CB-Abst participants who have biochemically-validated CB abstinence for two months because the goal is to study the effect of abstinence on change in mood and SI. If fewer than expected CB-Abst abstain from CB use for the full two months, we will form Helmert contrasts: those in CB-Mon (a), CB-Abst who do not abstain (b), and CB-Abst who abstain (c). The 1^st^ Helmert contrast will compare a to b+c and will be the intent to treat comparison. The 2^nd^ contrast will compare b to c, which corresponds to the post hoc sensitivity analysis of interest. Similar considerations will be made if participants in CB-Mon incidentally discontinue CB use during the study.

**Power analysis and justification of recruitment targets for the confirmatory cohort.** The R package ‘EMAtools’ (version 0.1.3; Kleiman, 2017) was used to determine the power for the proposed analyses. Preliminary analyses from the exploratory study found effect size estimates for significant effects ranged from 0.19 to 0.44, and that 77% of participants completed all phases of the study, completing on average 76% of all prompts. Estimates of the power were therefore computed to detect a weak effect (a Cohen’s d of .2) based on linear multi-level models using the nesting structure for the proposed EMA analyses and an intra-class correlation of .09. Table 1 shows the breakdown of estimates power based on the hypothesis being tested under two scenarios: 1) an ideal scenario with the full proposed number of participants and responses, and 2) a realistic scenario where 77% of participants complete 76% of entries.

Table 1: Power estimates by hypothesis and attrition scenario (ideal versus worse-case)

| Hypothesis | N (%) for sample size | N (%) of completed entries | Power |
| --- | --- | --- | --- |
| 1.1 - 1.2 | 200 (100%) | 112 (100%) | 99% |
|  | 154 (77%) | 85 (76%) | 93% |
| 2.1 - 2.2 | 200 (100%) | 224 (100%) | 99% |
|  | 154 (77%) | 170 (76%) | 94% |

1. **Monitoring and Quality Assurance**

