**Outcomes Monitoring**

Quality assurance procedures will include training of all study personnel (including psychology/psychiatry trainees) prior to initiation of the study and monitoring of subject enrollment and ensuring quality of data (source documentation and online in RedCap). Internal audits will be conducted under the supervision of the principal investigator, to assure that study data in RedCap are accurate and in agreement with source documentation, verify that consent for the study has been properly obtained and documented, and confirm that participants enrolled in the study meet inclusion and exclusion criteria. Any significant deviations from the protocol, including non-adherence to inclusion/exclusion criteria, errors in study procedures, or failure to complete assessments, will be reported to the Partners HRC as a protocol violation.

Participants will be terminated from this study if they fail to comply with study procedures, or if the opinion of the principal investigator, can no longer safely participate.

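### The main Aim 2 analysis selects CB-Abst on confirmed abstinence and makes intent-to-treat conditional on an undefined shortfall, so its group-by-phase comparison is not protected by randomisation

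*Protocol*

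**What the plan says.** Allocation (Protocol, Treatment Assignment and/or Randomization) is to 8 weeks of incentivised abstinence or to "non-contingent monitoring with no abstinence requirement (CB-Mon: n=100) using a 1:1 ratio in blocks of 6".

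Two paragraphs under Statistical Analysis set the Aim 2 analysis set:

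- Data analysis, Aim 2: "We will only include data for the CB-Abst group with confirmed abstinence for phases 2 – 3". The model has group, phase and group-by-phase terms. This paragraph places no limit on CB-Mon.
- Protocol non-adherence: analyses that involve phase 1 and/or phase 2 "will only consider CB-Abst participants who have biochemically-validated CB abstinence for two months because the goal is to study the effect of abstinence" on mood and SI.

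Intent-to-treat appears only in the second paragraph, and only on a condition: "If fewer than expected CB-Abst abstain from CB use for the full two months, we will form Helmert contrasts". The groups are CB-Mon (a), CB-Abst non-abstainers (b) and CB-Abst abstainers (c). The first "Helmert contrast will compare a to b+c and will be the intent to treat comparison". No contrast coefficients are given.

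On CB-Mon participants who stop using, the analysis text says only: "Similar considerations will be made if participants in CB-Mon incidentally discontinue CB use during the study". The conduct text says: "Individuals randomized to monitoring who incidentally stop using cannabis, or express an interest in discontinuing cannabis, will not be removed from the study".

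**The concern.** Staying abstinent for eight weeks is something participants do after randomisation, and the protocol itself ties it to the outcome: Hypothesis 1.1 is that worse mood precedes cannabis use on the same day. If so, the CB-Abst participants removed from the analysis may be those whose mood took a different course. CB-Mon keeps its own equivalents of both kinds of participant. A difference between the arms in mood change could then arise even if abstinence did nothing.

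The one comparison that would be free of this problem depends on an observed abstinence rate falling short of an unstated expectation. If abstinence meets that expectation, the document calls for no analysis of all randomised participants.

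The two paragraphs also disagree on scope. The first restricts phases 2 and 3. The second names phases 1 and 2 and requires two months of validated abstinence. Under the second, a participant's EMA data from week 1 after randomisation (phase 2) are kept or dropped according to behaviour up to seven weeks later.

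**Working it through.** **Inputs from the protocol.** 100 participants per arm; d = 0.2; intra-class correlation 0.09; realistic row of Table 1 for Hypotheses 2.1-2.2: 154 participants (77 per arm), 170 entries each. The abstinence share a and the difference D are not given, so ranges are assumed. Alpha is not stated for the power calculation; 0.05 two-sided is assumed.

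**The plan's own power figures.** I used a design-effect approximation for a difference between two arm means: deff = 1 + (m - 1) x 0.09, effective N = N x m / deff.

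| N, m | Approximation | Table 1 |
|---|---|---|
| 200, 112 | 99.5% | 99% |
| 200, 224 | 99.6% | 99% |
| 154, 85 | 97.4% | 93% |
| 154, 170 | 98.0% | 94% |

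The ideal rows agree. The realistic rows do not; they agree only if N is cut again, to about 117. The R package named in the protocol was not run, so the power figures below are approximate. Neither Aim 2 row takes anything off for excluded non-abstainers.

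**Selection bias.** Suppose abstinence has no effect. Let the natural mood change be M1 in would-be abstainers and M0 in the others, with D = M1 - M0.

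- Retained CB-Abst: M1.
- CB-Mon, by randomisation: a x M1 + (1 - a) x M0.
- Difference: M1 - a x M1 - (1 - a) x M0 = (1 - a) x D.

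| a | D = 0.1 | D = 0.2 | D = 0.3 |
|---|---|---|---|
| 40% | 0.06 | 0.12 | 0.18 |
| 60% | 0.04 | 0.08 | 0.12 |
| 80% | 0.02 | 0.04 | 0.06 |

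The range 0.02-0.18 SD is 10% to 90% of d = 0.2 (0.02/0.2 and 0.18/0.2).

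**Effect on type I error.** With 77 in CB-Mon, 77 x a in CB-Abst and m = 170: deff = 1 + 169 x 0.09 = 16.21, so each participant contributes 170/16.21 = 10.49 effective observations. At a = 50% and D = 0.2 the bias is 0.10. The standard error is sqrt(1/(38.5 x 10.49) + 1/(77 x 10.49)) = 0.061, and the chance of a nominally significant result is about 38%. At a = 80% and D = 0.2 it is about 12%.

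**Cost of intent-to-treat.** If abstainers shift by 0.2 and non-abstainers by 0, the arm difference is 0.2 x a. With 77 per arm the standard error is sqrt(2/(77 x 10.49)) = 0.050.

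| a | Difference | Approximate power |
|---|---|---|
| 90% | 0.18 | 95% |
| 75% | 0.15 | 85% |
| 50% | 0.10 | 52% |
| 30% | 0.06 | 22% |

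With the smaller N of 117 that matches the printed 94%, the values at 75% and 50% are about 75% and 42%.

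**Helmert weights.** Under equal-weight coding the first contrast targets (b + c)/2; intent-to-treat targets (1 - a) x b + a x c. With c = 0.2 and b = 0 the equal-weight value is 0.10 at any a, against 0.06 at a = 30%, 0.10 at 50% and 0.15 at 75%. If b+c means the pooled arm, the two are identical.

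**The case against.** The best defence is that the protocol states its aim: it wants the effect of abstinence, not of being assigned to it, and an intent-to-treat contrast answers a different question with less power. Hypotheses 2.1 and 2.2 are also worded as changes between phases within each arm, so stable differences between participants largely cancel. Both points stand in part. They justify reporting an abstainer analysis, and they are why D is defined on mood change and not on level. They do not remove bias from differential change, which is what Hypothesis 1.1 makes plausible.

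The figure for expected abstinence may sit in a SAP that is not shown. Even so, the protocol itself makes the by-arm comparison conditional. The sentence on CB-Mon participants who stop using shows the issue was noticed, but it specifies nothing, and excluding those participants would add selection in the second arm.

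Four stronger readings are tempting and not supported:

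- That the fallback contrast is mis-weighted. No coefficients are stated, and b+c can be read as the pooled CB-Abst arm, which is correct.
- That the rule on ending participation for failure to comply would remove non-abstainers. The protocol does not call cannabis use non-compliance, and the planned comparison of b with c presupposes that those participants supply data.
- That the group contributing to phase 1 differs from that in phases 2 and 3. This follows only if the Aim 2 paragraph is read without the non-adherence paragraph.
- That the bias favours the hypotheses. No document supports a direction. If participants with a better mood course are the ones who abstain, that would help Hypothesis 2.2 but work against the week-1 worsening predicted by Hypothesis 2.1.

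**Conclusion.** The concern holds for the main Aim 2 analysis. As written, its group-by-phase comparison rests on a CB-Abst group selected after randomisation, and the only by-arm comparison hangs on an undefined trigger. The bias is (1 - a) x D: 0.02-0.18 SD over the assumed ranges, against d = 0.2. Those ranges are mine, so the figures show what modest selection could do and are not an estimate of what will happen. The disagreement over scope between the two paragraphs, and the dependence of week-1 data on later abstinence, follow from the text alone.

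A reader might infer that the trial has lost its randomised comparison altogether. That goes too far: a by-arm contrast is named, and if pooled it would be valid. It is not guaranteed to be run.

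**What to change.** 1. In Data analysis, Aim 2, state that the group-by-phase analysis is run in all randomised participants by assigned arm, with all available phase 1-3 EMA data, whatever the abstinence rate. Code it with the arm indicator. That removes the undefined trigger and any doubt about Helmert weights.
2. Report the confirmed-abstainer comparison beside it, labelled as a non-randomised analysis of the effect of abstinence.
3. Reconcile the Aim 2 and Protocol non-adherence paragraphs on which phases are restricted, on whether the two-month rule governs phase 2 data, and on what is done with CB-Mon participants who stop using.

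The cost is wording in two paragraphs and one additional model fit per outcome. The real downside is dilution, as tabulated: about 85% power at 75% abstinence and 52% at 50%, under the stated assumptions. Partial reductions in use among non-abstainers would change these figures.

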SI are temporarily relieved and stabilized through acute cannabis use (i.e., negative reinforcement).

*Hypothesis 1.1:* Negative mood will predict subsequent same-day cannabis use events as well as greater self-reported motivation to use cannabis for mood improvement (EMA Phase 1; Baseline as Usual).

*Hypothesis 1.2:* Negative mood and SI reported within one hour following cannabis use will be lower in intensity and less variable than mood and SI reported during same-day random-prompt EMA reports occurring ≥1 hours since last cannabis use (EMA Phase 1; Baseline as Usual).

*Hypothesis 1.3 (exploratory):* There will be within-subject correlates (e.g., concurrent other substance use, social context of use) and between-subject factors (e.g., cannabis use and depression severity, history of suicidal behavior) that moderate relationships between acute cannabis use and mood and SI.

**Aim 2:** To test if negative mood and SI decrease in overall (mean) levels and variability after cannabis

wash-out.

*Hypothesis 2.1:* Among CB-Abst but not CB-Mon, negative mood and SI reported during random prompt EMA reports will intensify and become more variable throughout the first week of sustained cannabis withdrawal (EMA Phase 2; Randomized Withdrawal) compared to random, non-use events during baseline cannabis use as usual (EMA Phase 1; Baseline as Usual).

*Hypothesis 2.2:* Negative mood and SI reported during EMA random prompts after 8 weeks of abstinence (EMA Phase 3; Randomized Sustained Abstinence) will be lower in intensity and variability than negative mood and SI reported during EMA random prompts occurring during random, non-use events during baseline cannabis use as usual (EMA Phase 1; Baseline as Usual) and withdrawal (EMA phase 2; Randomized Withdrawal). There will be no difference in mood or SI intensity or variability across the 3 EMA phases in CB-Mon.

1. **General Description of Study Design**

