**Inclusion Criteria**

1. Ages 12-18;
2. Current daily or near daily cannabis use (i.e., use ≥ 4 days per week on average; Timeline Followback);
3. Score ≥ 5 on PHQ-9;
4. Access to an internet-capable smartphone (iOS or Android);
5. Provision of at least 1 collateral contact for risk monitoring;
6. Provision of informed assent (or consent if 18 years) and parent/guardian consent if <age 18;
7. Approximately 50% response rate to EMA prompts during the first EMA phase (Baseline as Usual);
8. No immediate plan to discontinue cannabis use in the next 3 months;
9. Positive toxicology result for cannabis on baseline urinalysis.

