**Screening (V0):** School-wide screening will take place on site and at the participating schools (as part of #2021P001873), and/or over the phone. Data will be collected during the screening to determine eligibility for the study.

*Measures to be completed by participants:*

- School-wide screening instrument (as part of #2021P001873; only for participants recruited through schools)
- Telephone screener
- Universal screener (as part of #2024P002895)

**Baseline Visit (V1):** Participants will attend an approximately 3-hour baseline visit to be conducted on the campus of the participating school, at a local library, at Massachusetts General Hospital, or virtually via video conferencing (via MGB-approved video conference platforms like Microsoft Teams or zoom). The baseline visit will initiate a 2 week-long baseline phase involving smartphone EMA during which they will use cannabis per usual to quantify the temporal relationship between use and mood and SI, and the within- (e.g., concurrent other substance use, social contexts) and between-subject factors (e.g., severity of cannabis use, depression, and SI) that moderate these linkages. We will ensure that this 2-week baseline phase does not coincide with when there are anticipated major deviations from typical patterns of cannabis use (e.g., family vacation, exam week).

*Eligibility confirmation to be completed prior to obtaining consent:*

Patient Health Questionnaire-9 (PHQ-9)

*Measures to be completed by participants following consent:*

- Timeline Followback Interview (TLFB)
- Substance Use History
- Marijuana Craving Questionnaire – Short form (MCQ-SF)
- Cannabis Withdrawal Scale (CWS)
- Marijuana Motives Measure (MMM)
- Drug Testing
- Ecological Momentary Assessment (EMA) Training
- The Reasons of Living for Adolescents (RFL-A)
- Self-injurious Thoughts and Behaviors Interview-Revised (SITBI-R)
- Child Behavior Checklist Youth Self Report (CBCL)
- Columbia Suicide Severity Rating Scale (C-SSRS)
- Pittsburgh Sleep Quality Index (PSQI)
- Mini International Neuropsychiatric Interview (MINI) Kid 7.0.2: Cannabis Use Disorder and Major Depressive Episode
- Beck Anxiety Inventory (BAI)
- Alcohol Use Disorder Identification Test (AUDIT)
- The Cannabis Use Disorder Identification Test (CUDIT)
- Penn State Electronic Cigarette Dependence (ECDI)
- Connors ADHD Self-Report Index (ASRI)
- Psychiatric History
- Concomitant Medications
- Demographics
- *Fitbit Set-up

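### Aim 2 words H2.1 and H2.2 as a change in CB-Abst plus no change in CB-Mon, and does not name the group-by-phase interaction as the deciding test

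*Protocol*

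**What the plan says.** Aim 2 is the part of the Protocol that uses the randomisation. Under Data analysis, Aim 2, each hypothesis has two limbs. For H2.1, CB-Abst rises in mean and variability from phase 1 to phase 2. For H2.2, CB-Abst falls "during phase 3 compared to phase 1, while CB-Mon will show no differences between phases". Specific Aims and Objectives has the same structure and ends H2.2 with "There will be no difference in mood or SI intensity or variability across the 3 EMA phases in CB-Mon". That version of H2.2 also compares phase 3 with phase 2, which the analysis section does not.

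The analysis section lists predictors for group, for phase (2 vs 1 and 3 vs 1) and "c) terms for the group by phase interactions", and places all of them on the residual variance term as well. It does not say which of these coefficients decides H2.1 or H2.2. The Multiple testing paragraph adjusts across six negative affect measures within each hypothesis, again without naming the coefficient that supplies the p-value.

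Two other statements matter. The analysis set is restricted: "We will only include data for the CB-Abst group with confirmed abstinence for phases 2 – 3". Under Protocol non-adherence, a Helmert contrast of CB-Mon with all of CB-Abst "will compare a to b+c and will be the intent to treat comparison", but it is formed only if fewer CB-Abst participants abstain than expected. The randomisation section calls the trial a "2-arm, within-subject, parallel group design".

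**The concern.** A randomised monitoring arm is there so that change over time unrelated to abstinence can be subtracted. A hypothesis worded as one arm changing and the other not changing does no subtraction. It compares two significance results, and a non-significant CB-Mon contrast does not show that nothing changed.

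Some change common to both arms is plausible. Participants enter with "Score ≥ 5 on PHQ-9", and the Protocol's benefits section allows that monitoring itself may improve mental health. If both arms drift down a little, CB-Abst may reach significance and CB-Mon may not, with no effect of abstinence. If both drift down more, CB-Mon changes too and the predicted pattern fails, even where CB-Abst truly falls further. The stated hypotheses could therefore be called supported without an arm difference, or refuted with one.

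**Working it through.** **Inputs from the Protocol.** 100 per arm; 77% of participants and 76% of prompts completed; effect d = 0.2; intra-class correlation 0.09; 112 scheduled prompts in phase 1 and 224 over all phases (Table 1), which leaves 56 in each of phases 2 and 3; phase 1 = days 0-14, phase 2 = days 14-21, phase 3 = days 63-70.

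**Assumptions.** Two-sided 0.05 tests. Between-person SD of true phase change 0.3 to 0.7, and shared shift 0 to -0.3, both in outcome SDs. The Protocol states none of these.

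**Step 1: reproduce Table 1.** Effective N = participants × completed prompts / [1 + 0.09 × (scheduled prompts - 1)], split into two equal groups.
- H2 ideal: 200 × 224 / 21.07 = 2126, or 1063 per group. Power = Φ(0.2/√(2/1063) - 1.96) = 99.6% (stated 99%).
- H2 realistic: 154 × 170 / 21.07 = 1243, or 621 per group. Power = 94.1% (stated 94%).
- H1 rows, same formula: 99.5% and 93.2% (stated 99% and 93%).

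Table 1 is therefore the power of one two-group contrast. It is neither the two-limb pattern nor the interaction.

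**Step 2: the two-limb pattern with no abstinence effect.** Let both arms share a true fall of δ standard errors, with equal precision. Then P(pattern) = Φ(δ - 1.96) × [Φ(1.96 - δ) - Φ(-1.96 - δ)].

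| δ | CB-Abst significant | CB-Mon not significant | Pattern |
|---|---|---|---|
| 0 | 0.025 | 0.950 | 0.024 |
| 1 | 0.169 | 0.830 | 0.140 |
| 1.5 | 0.323 | 0.677 | 0.218 |
| 1.96 | 0.500 | 0.500 | 0.250 |
| 2.5 | 0.705 | 0.295 | 0.208 |

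The maximum is 25%. On the model scale a shared shift cancels from the interaction, so its false-positive rate in the predicted direction stays at 2.5% for every δ. With 77 per arm, 1.96 standard errors is 1.96/√77 = 0.22 SD of person-level phase change.

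**Step 3: both directions of error.** Take 77 per arm, 76% of prompts (85 in phase 1, 43 in phase 3) and an SD of true change of 0.5. Variance per participant = 0.25 + 0.91 × (1/85 + 1/43) = 0.282; standard error per arm = √(0.282/77) = 0.0605. The H2.1 column uses the same variance, since phase 2 is also one week.

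| Shared shift | H2.2 pattern, no effect | H2.2 pattern, true effect -0.2 | H2.1 pattern, true effect +0.2 |
|---|---|---|---|
| 0 | 2.4% | 86.5% | 86.5% |
| -0.05 | 11% | 86% | 61% |
| -0.10 | 24% | 62% | 23.5% |
| -0.20 | 8% | 9% | 0.2% |
| -0.30 | 0.1% | 0.1% | not computed |

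**Step 4: power of the interaction at d = 0.2.** Its standard error is √2 × 0.0605 = 0.0856, so power = Φ(0.2/0.0856 - 1.96) = 64.7%, whatever the shared shift. For SDs of true change of 0.3 / 0.5 / 0.7:
- 77 per arm: 94.5% / 64.7% / 40.4%.
- 100 per arm, all prompts: 98.7% / 77.0% / 50.5%.
- No between-person variation in change: over 99.9%.

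The Protocol's own effective-N approach with four equal cells has standard error √(4/(N/4)). This gives about 63% with N = 2126 and 42% with N = 1243.

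**The case against.** The strongest reply is that the contrast is already planned. The Statistical models paragraph says predictors are added to test the hypotheses, and for Aim 2 these include the interactions. A statistician would naturally read them as the test, and an analysis plan could say so. This stands in part: the model needs no change, and a reader who infers that the trial has no between-arm comparison would be wrong. What remains is that the Protocol fixes the hypotheses, in two places, in a form that the interaction does not test.

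Second, the Protocol never states a rule of significant in one arm and not in the other. That is correct. The percentages describe one inferred reading and are not the trial's type I error.

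Third, the CB-Mon limb is a partial safeguard. This also stands: under the Step 3 assumptions false support falls to 8% at a shared shift of -0.20 and 0.1% at -0.30.

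Three stronger readings are tempting and not supported:
- That natural improvement over ten weeks could produce both results. H2.1 compares days 14-21 with days 0-14 and predicts a rise, so improvement can only hide it.
- That the PHQ-9 threshold guarantees regression to the mean in the outcome. The outcome is EMA, collected in the two weeks after that score, so some regression may already fall inside phase 1.
- That the scheduling rule for baseline ("We will ensure that this 2-week baseline phase does not coincide with when there are anticipated major deviations from typical patterns of cannabis use") biases the arm comparison. The Protocol states no such rule for phases 2 and 3, but randomisation gives both arms the same expected calendar exposure. No calendar check is needed on this ground.

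**Conclusion.** The point holds as a fault in how the hypotheses are tied to the model. H2.1 and H2.2 are worded as within-arm change plus an unmargined null in CB-Mon, and the interactions that would remove a shared time trend are estimated but not named as deciding. On the inferred two-limb rule, false support for H2.2 reaches about 25% at worst under modest shared change, against 2.5%. Larger shared change makes the rule miss a real effect. For H2.1 the risk from improvement is masking only. These sizes rest on two-sided 0.05 tests, equal precision in the two arms, and assumed shifts and SDs of change.

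One limit remains after correction. While CB-Abst data in phases 2 and 3 are restricted to confirmed abstinence, even the interaction compares a selected part of one arm with all of the other, so it is not a fully randomised comparison.

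**What to change.** In Specific Aims and in Data analysis, Aim 2:
- State that H2.1 is decided by the group × (phase 2 vs 1) contrast.
- State that H2.2 is decided by the group × (phase 3 vs 1) contrast, and also by group × (phase 3 vs 2), since Specific Aims includes that comparison. The latter is the difference of the two interaction terms already in the model.
- Apply this to both mean and variability, and name these p-values as the ones entering the false discovery rate step.
- Report within-arm phase changes with confidence intervals as description, and drop an unchanged CB-Mon arm as a condition of support.
- Report the same contrasts for all randomised participants, whether or not abstinence falls short of expectation.

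The model stays as it is. The cost is precision: with equal arms the interaction's standard error is √2 times that of a within-arm change. In the Step 3 setting with no shared shift, its power is 64.7%, where the two-limb pattern would appear 86.5% of the time. The 99% and 94% for H2.1-2.2 in Table 1 therefore cannot be carried over. They must be restated for the interaction, with the assumed SD of phase change given.
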